##### Treatment Adherence

Number of meditations completed, number of days with at least one meditation completed, and total time meditated in minutes will be used as behavioral measures of treatment adherence. This information is tracked by the Ten Percent Happier app and will be obtained by asking participants in the intervention group to share a screenshot of their app profile via text message. Previous studies have shown that this methodology allows researchers to obtain accurate behavioral indicators of treatment adherence [60,77]. These behavioral indicators will be collected at midtreatment and posttreatment.

## Results

Recruitment began in October 2021. This study will use multilevel modeling, a statistical methodology that allows time-varying predictors and handling dependence among repeated observations. We will examine changes in primary outcomes (ie, stress, anxiety, depression), hypothesized mediators (ie, mindfulness trait, self-compassion, experiential avoidance, rumination, emotion suppression), and treatment effects from baseline to midtreatment and posttreatment, and from midtreatment to posttreatment within each group. Test of mean differences will be calculated by fitting models with group condition (ie, intervention vs control) as the predictor, time as a within-group factor (ie, baseline, midtreatment, posttreatment), and a group-by-time interaction. To explore whether changes in primary outcomes are mediated by changes in the hypothesized mechanism of change, we will conduct mediation analyses. Relevant demographic variables (eg, income, age, gender) will be added to the models as covariates. These models will include random intercepts to capture potential differences in the starting points of each outcome and an autoregressive error structure to account for dependence among repeated measures. Given the relatively small sample size in this study, random slopes will be fitted when possible. Although our primary interest is in group-by-time interactions corresponding to differential treatment effects, should significant interactions or main effects be found, follow-up contrasts can be used to examine within-group changes over time and between-group differences at each time point.

Considering issues of attrition and their potential effects on statistical significance and treatment effect sizes in app-based mindfulness meditation research [49], we will examine data using both intention-to-treat and per-protocol analyses [78]. In intention-to-treat analyses, group comparisons include all patients originally allocated after randomization, regardless of participant adherence to the intervention or withdrawal. Missing data will be handled using the last-observation-carried-forward method, which is considered a conservative approach. In per-protocol analyses, group comparisons include only those participants who completed the treatment as planned originally. Measures of treatment acceptability, satisfaction, and adherence will be examined by calculating descriptive statistics.

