## Methods

### Participants

A power analysis using G*Power [58] indicated that, based on 2 groups (ie, control vs active treatment), 3 repeated measurements (ie, baseline, midtreatment, posttreatment), a conservative *r*=.60 correlation among repeated measures, and a small *d*=0.2 treatment effect size, a sample of n=54 provides 95% power to detect a treatment by time interaction using the most conservative outcome in this study. Considering recent meta-analytic work suggesting an approximately 24% attrition rate in short-term (ie, 4 weeks or less) mindfulness meditation app trials with at-risk samples [49], we plan to recruit 80 POC individuals for this study.

Individuals interested in participating in this study will complete an online screening questionnaire using Qualtrics, a platform that is smartphone compatible. For study inclusion, participants are required to (1) self-identify as a member of a POC group (eg, Black/African American, Asian/Asian American/Pacific Islander, Latinx, Native American/Native Alaskan, multiracial, other), (2) report experiencing elevated levels of race-related stress (ie, a score of 55 or higher on the Index of Race-Related Stress–Brief [IRRS-B] [4] or a score of 12 or higher on the Multicultural Discrimination Module [MDM] [59]), (3) speak and read English, (4) not receive psychological services currently (ie, individual or group therapy, any type of counseling), (5) not have practiced mindfulness meditation for more than 2 hours in the month prior to study commencement, (6) own a smartphone with access to the internet, (7) be willing to install the mindfulness meditation app and accept daily notifications and text reminders, and (8) be aged 18 years or older.

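### The planned group-by-time model is valid, but it uses baseline inefficiently and its primary test is not aimed at the end of the 4-week programme

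*Protocol article*

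**What the plan says.** The Results section of the protocol article describes "fitting models with group condition (ie, intervention vs control) as the predictor, time as a within-group factor" (baseline, midtreatment and posttreatment) and a group-by-time interaction. It says that the interactions are the primary interest. On the remaining structure it says: "These models will include random intercepts to capture potential differences in the starting points of each outcome", with autoregressive errors and random slopes where they can be fitted. Income, age and gender are given as examples of covariates; the baseline value of the outcome is not mentioned. Between-group differences at each time point appear as follow-up contrasts that may be used if an interaction or main effect is significant. No single primary time point is named.

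The Participants section powers the same test. It uses "A power analysis using G*Power", with "2 groups (ie, control vs active treatment") and "3 repeated measurements (ie, baseline, midtreatment, posttreatment"), and states that n=54 "provides 95% power to detect a treatment by time interaction using the most conservative outcome in this study".

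**The concern.** Two features of the stated model work against a small trial.

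- **Use of baseline.** Baseline is one of the three outcomes and the group term is free at baseline, so the week-4 treatment effect is the arm difference in change scores. A change score subtracts the whole baseline difference, whereas the efficient weight is the baseline-to-week-4 correlation. The random intercept describes variation between people; it does not supply that adjustment between arms.
- **Target of the test.** The Discussion gives the main goal as whether the intervention reduces stress, anxiety and depression compared with control. A three-level time factor crossed with two arms gives an interaction with 2 degrees of freedom, which responds to any departure from parallel profiles and so does not single out the end of the programme.

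At stake is power in a sample that the article itself calls relatively small and in which it expects about 24% attrition. The interpretation of a significant result is also at stake.

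**Working it through.** **Inputs.** From the Participants section: 40 per arm, three measurements, r=.60 ("60 correlation among repeated measures"), and an effect of 0.2 ("0.2 treatment effect size"). Assumed here, because the article does not give them: alpha .05, equal variances across visits, and a week-4 effect of 0.5 SD for the power comparison.

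**1. The plan's own figure.** For the repeated-measures interaction, the noncentrality is λ = f²·N·m/(1−r), with 2 and 2(N−2) degrees of freedom. With f=0.2, N=54, m=3 and r=.60, λ = 0.04×54×3/0.40 = 16.2 and power is 0.954. At N=52 power is 0.946, so 54 is the smallest even N that reaches 95%. The stated figure is reproduced with a 2-degree-of-freedom interaction and 0.2 entered as Cohen's f. The article labels 0.2 as d; that is a separate matter and nothing below depends on it.

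**2. Precision of the week-4 contrast**, in units of 2σ²/n:

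- Free baseline means (change score): 2(1−r) = 2×0.40 = 0.80
- Common baseline mean, or baseline as covariate: 1−r² = 1−0.36 = 0.64
- Ratio: 2(1−r)/(1−r²) = 2/(1+r) = 2/1.60 = 1.25

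With σ=1 and 40 per arm, the standard errors are √(0.05×0.80) = 0.200 and √(0.05×0.64) = 0.179. The variance ratio is 0.80, so 80 participants carry the information of about 100.

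| Baseline-to-week-4 correlation | Gain, 2/(1+r) |
|---|---|
| .36 (pure AR(1), adjacent r=.60) | 1.47 |
| .50 | 1.33 |
| .60 | 1.25 |
| .70 | 1.18 |
| .80 | 1.11 |

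When the baseline slope is estimated, 20,000 simulated trials per setting at r=.60 with 27 to 40 per arm gave a ratio of 1.22 to 1.23.

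**3. What the planned interaction detects.** For arm differences d at weeks 0, 2 and 4, f² is the variance of d across the three visits divided by 4. With N=80 and r=.60, λ = f²×80×3/0.40 = 600f², on 2 and 156 degrees of freedom.

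| Profile (weeks 0, 2, 4) | f² | λ | Power |
|---|---|---|---|
| Linear growth: 0, 0.25, 0.5 | 0.01042 | 6.25 | 59% |
| Full by week 2: 0, 0.5, 0.5 | 0.01389 | 8.33 | 73% |
| Week 4 only: 0, 0, 0.5 | 0.01389 | 8.33 | 73% |
| Week 2 only: 0, 0.5, 0 | 0.01389 | 8.33 | 73% |

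The last two rows are identical: the test cannot tell a transient week-2 effect from a week-4 effect of the same size.

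**4. Single-degree-of-freedom week-4 contrasts, same 0.5 SD effect.** Change score: 0.5/0.200 = 2.50, power 69%. Baseline-adjusted: 0.5/0.179 = 2.80, power 79%. Both are the same for the first three profiles, since only week 4 enters the effect.

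**5. With about 30 per arm and linear growth** (normal approximation): planned interaction 48%, change contrast 58%, baseline-adjusted contrast 68%.

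**The case against.** The strongest reply is that nothing here is an error. Group, time and group-by-time is unbiased under randomisation, the power calculation and the analysis concern the same test, and an article may leave refinements to a fuller plan. The validity point stands. It does not remove the finding, because the article does state the model and the target, and a better use of data already collected is available.

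Several limits on the size also stand:

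- A reader might infer that the gain is at least 25%. The documents do not support that. The article calls .60 conservative, so a higher correlation and a smaller gain are what its authors expect. Its last-observation-carried-forward rule pushes the same way: if 24% leave after baseline with baseline carried forward, the correlation becomes about .76×.60 + .24×1 = .70 and the gain about 18%. The 47% figure needs pure AR(1) decay, whereas the plan combines autoregressive errors with a random intercept, so 47% is an upper bound.
- A reader might say that baseline is wasted. It is not: at r=.60 the change contrast has variance 0.80, against 1.00 for a comparison of week-4 values alone.
- The article does not write 2 degrees of freedom. That is inferred from the three-level factor, although it is what reproduces n=54.
- The 2-degree-of-freedom test is not always the weaker one. For an effect that is full by week 2 or appears only at week 4, its 73% exceeds the 69% of an unadjusted week-4 change contrast.
- The follow-up contrasts could answer the week-4 question, but they are optional and depend on a significant result first.

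A reader might also infer that the change is free of risk. The documents do not support that either. Under Procedures, baseline is placed at randomisation or week 0. Under Participants, randomisation happens in the onboarding contact. Under Descriptive Outcomes, the acceptability and satisfaction questionnaires go to the intervention group only, and at baseline, which suggests that allocation may already be known. If so, randomisation does not guarantee equal baseline means, and imposing them could bias the contrast.

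**Conclusion.** The point holds as one of efficiency and aim; the planned analysis is valid. At the protocol's r=.60, a baseline-adjusted week-4 contrast has the precision of about 25% more participants, or 22% to 23% with an estimated slope. Over the plausible correlations the gain runs from about 11% (r=.80) to at most 47% (pure AR(1) decay). At an assumed 0.5 SD week-4 effect with complete data on 80, power is 79%, against 59% to 73% for the planned interaction, depending on how the effect develops. In sample-size terms at 80% power and r=.60, the combined gain is 53% for linear growth but only 15% if the effect is full by week 2 or appears only at week 4.

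These figures assume alpha .05, equal variances across visits and, for the constrained or adjusted estimate, a baseline completed before allocation is known. The article leaves that last condition open. No fault is shown in the planned covariance structure; an unstructured covariance or small-sample degrees of freedom would be optional.

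**What to change.** 1. First confirm and state whether the baseline questionnaires are completed before allocation is known, and reconcile this with the intervention-only questionnaires listed at baseline.
2. If they are, name as the primary test, for each of stress, anxiety and depression, the arm difference at week 4 adjusted for the baseline value of that outcome, or the same contrast from a longitudinal model with a common baseline mean. Report the midtreatment contrast as secondary.
3. If baseline follows allocation, do not impose equal baseline means. Use the 1-degree-of-freedom week-4 change contrast as primary. This still ties the test to the end of the programme, but without the gain in precision: 69% power in the example above.

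The cost is a sentence or two of model specification, settled before the data are analysed, with no new data collection. The downside is that an effect seen only at midtreatment no longer counts towards the primary test.

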### Procedures

Participants are being recruited through social media, sending emails to relevant groups, and posting physical flyers in communities with significant POC representation. Considering the current COVID-19 pandemic, data are being collected using an online procedure (ie, Qualtrics) at baseline (ie, randomization or week 0), midtreatment (ie, 2 weeks after randomization), and posttreatment (ie, 4 weeks after randomization) via online questionnaires. These assessments were piloted among POC to improve survey clarity and minimize participant fatigue before starting recruitment. These remote assessment strategies have shown to be effective in app-based intervention research with low-income POC [53].

Participants in both conditions will receive a free subscription to the mindfulness meditation app intervention as an incentive to participate. Additionally, participants will be compensated with US $10, $15, and $25 for completing baseline, midtreatment, and posttreatment questionnaires, respectively. There is evidence that monetary compensation significantly reduces attrition in app-based mindfulness meditation studies [49]. Figure 1 shows the study design flow.

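### Three visits support random slopes plus autoregressive errors only weakly, and the fallback can misstate the standard errors of the week 0-2 and 2-4 changes; an unstructured covariance avoids both

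*Protocol article*

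**What the plan says.** Under Results, the protocol article describes one multilevel model for all outcomes. The mean part has group, "time as a within-group factor (ie, baseline, midtreatment, posttreatment"), and their interaction. The covariance part has "random intercepts to capture potential differences in the starting points of each outcome and an autoregressive error structure". The text then adds: "Given the relatively small sample size in this study, random slopes will be fitted when possible". It does not say whether such a slope would be linear in time or placed on the time factor.

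The same section says changes will be examined "from baseline to midtreatment and posttreatment, and from midtreatment to posttreatment within each group", so the changes over weeks 0-2, 0-4 and 2-4 are all named. It gives the group-by-time interaction as the primary interest and offers follow-up contrasts as an option after a significant interaction or main effect. Missing values in the intention-to-treat analysis are filled by last observation carried forward.

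The Participants section plans on "3 repeated measurements (ie, baseline, midtreatment, posttreatment") and assumes "a conservative *r*=.60 correlation among repeated measures". Procedures places the follow-up visits at "midtreatment (ie, 2 weeks after randomization), and posttreatment (ie, 4 weeks after randomization"), so the three visits are equally spaced.

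**The concern.** The text ties the feasibility of random slopes to the small sample, but the number of visits is the tighter limit. Three visits give a 3x3 covariance matrix with six distinct elements, and a slope added to a random intercept and autoregressive errors nearly uses these up or exceeds them. Whether a slope proves feasible is then decided by how the software converges, separately for eight outcomes (three primary, five secondary) in two analysis sets, or up to 16 fits.

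If the slope is dropped, a random intercept with autoregressive errors remains. With equally spaced visits that structure gives the first and second two-week changes the same variance. If the true variances differ, one change gets a standard error that is too small and the other one that is too large. The plan names both changes as things it will examine. Its own carry-forward rule can also produce unequal variances, because it copies week-2 values into week 4.

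**Working it through.** **Inputs.** From the documents: three visits at weeks 0, 2 and 4; 80 people, 40 per arm; a common correlation of .60; 24% attrition; carry-forward. Assumed: autoregression of order 1, two-sided 5% tests, baseline SD of 1, dropout unrelated to outcome, no mean change in the carry-forward cases, and every correlation pattern other than the common .60.

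**The plan's own figure.** The article gives no figure for the covariance model. Its nearest figure is n=54 for 95% power. This reproduces with λ = f²·N·m/(1−r) = 0.04×54×3/0.40 = 16.2 on 2 and 104 df, power 0.954, if 0.2 is entered as Cohen's f although it is labelled d (a separate matter). That calculation uses one common correlation, which is the case where the fallback model is correct.

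**Step 1, parameters against six covariance elements.**
- Random intercept (1) + AR(1) (2) = 3: identified.
- Random intercept and linear slope with their covariance (3) + AR(1) (2) = 5: identified (rank 5 at every AR correlation tried), one element to spare.
- Random effects on the three-level factor (6) + AR(1) (2) = 8: not identified at any sample size.

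**Step 2, how well 80 people support the five-parameter model (complete data).** The expected standard error of the AR correlation is about 0.51-0.83. For a slope variance of 0.05, the standard error is 0.07-0.15. In 300 simulated fits per scenario, a boundary was reached in 63% (true common r=.60, no slope), 50% (slope variance .05) and 40% (slope variance .10, AR correlation .3).

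**Step 3, what the fallback forces.** With intercept variance τ², residual variance σ² and AR correlation ρ, Var(week 2 − week 0) = Var(week 4 − week 2) = 2σ²(1−ρ). In the cases below, the limiting fit sets this to the mean of the two true variances. The actual size of a nominal 5% test is 2Φ(−1.96·√(modelled/true)).

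Worked case: r=.60, all 24% dropping out after week 2, carried forward. The true 0-2 variance is 2(1−.60) = 0.80. The true 2-4 variance is 0.76×0.80 = 0.608, because carried-forward people have zero change. The modelled variance is (0.80+0.608)/2 = 0.704. Size for 0-2: √(0.704/0.80) = 0.938, giving 6.6%. Size for 2-4: √(0.704/0.608) = 1.076, giving 3.5%.

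| Truth (correlations 0-2, 2-4, 0-4) | Var 0-2 | Var 2-4 | Modelled | Size 0-2 | Size 2-4 |
|---|---|---|---|---|---|
| common .60, equal SDs, complete data | 0.80 | 0.80 | 0.80 | 5.0% | 5.0% |
| .55, .65, .60 | 0.90 | 0.70 | 0.80 | 6.5% | 3.6% |
| .60, .70, .55 | 0.80 | 0.60 | 0.70 | 6.7% | 3.4% |
| .60, .75, .55 | 0.80 | 0.50 | 0.65 | 7.7% | 2.5% |
| .50, .70, .50 | 1.00 | 0.60 | 0.80 | 8.0% | 2.4% |
| .55, .80, .50 | 0.90 | 0.40 | 0.65 | 9.6% | 1.2% |
| common .60, SDs 1, 1.1, 1.2 | 0.890 | 1.066 | 0.978 | 4.0% | 6.0% |
| common .60, carry-forward, 12% before and 12% after week 2 | 0.704 | 0.608 | 0.656 | 5.8% | 4.2% |
| common .60, carry-forward, 24% after week 2 | 0.80 | 0.608 | 0.704 | 6.6% | 3.5% |
| common .60, carry-forward, 24% before week 2 | 0.608 | 0.608 | 0.608 | 5.0% | 5.0% |

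The rising-SD row reverses the direction. By symmetry, so does a 0-2 correlation above the 2-4 correlation.

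**Step 4, what is not affected.** The model-to-true standard error ratio for the week 0-4 change stayed at 0.99-1.01 throughout. The overall 2-df interaction test ran at 5.1-5.6% in the patterns .60/.70/.55, .60/.75/.55 and .55/.80/.50.

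**Step 5, finite-sample check.** In 1,500 simulated trials of 40 per arm with complete data, the fallback's 0-2 test ran at 7.3% (.60/.75/.55) and 9.2% (.55/.80/.50). An unstructured covariance gave 4.3% and 4.9%.

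**The case against.** A reader might infer that the stated model cannot be estimated. The documents do not support that. Time is coded as a factor for comparing means, but the article never puts the random slope on that factor, and a slope ordinarily means linear time, which is identified.

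A reader might also infer that early effects will be declared too often and late ones missed. That direction comes from assumed correlations. Under the article's single r=.60 with equal SDs and complete data there is no error, and rising SDs reverse the pattern.

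The two halves of the point are also largely independent. A linear slope uncorrelated with the intercept adds the same variance to both adjacent changes, and dropping a true linear slope moved their standard errors by 0.5% or less in the cases tried. Boundary fits are expected when there is no slope to find, so reducing to the simpler model is then sensible. The sizes above also treat the contrasts as unconditional, whereas the article presents follow-up contrasts as optional after a significant result.

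All of this stands, and it limits the point. A criterion for keeping or dropping slopes may well sit in an analysis plan that is not shown, so its absence is not the complaint. What remains concerns what the article does state: a covariance rule that three visits support poorly, and a fallback that imposes equality on two changes the article says it will examine. The carry-forward rule breaks that equality even at the article's own r=.60, once people drop out after week 2.

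**Conclusion.** The point holds as a minor one. Random slopes added to a random intercept and AR(1) errors are weakly identified if linear (5 parameters for 6 elements, boundary fits in roughly 40-63% of simulated trials of 80) and not identified if placed on the time factor (8 for 6). The stated rule therefore lets convergence choose the model for each outcome.

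The fallback can misstate the standard errors of the week 0-2 and 2-4 changes in opposite directions, in either order, when adjacent correlations or visit SDs differ. Sizes of 6.5-9.6% and 1.2-3.6% rest on assumed correlations and should be read as illustrations. The part that rests on the article's own r=.60 and 24% attrition is smaller: 5.8-6.6% and 3.5-4.2% when half or all of the dropout follows week 2, and no error when all of it comes earlier.

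It would be wrong to conclude that the trial's main test is compromised: the overall group-by-time test and the week 0-4 change are little affected.

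**What to change.** For every outcome and both analysis sets, replace the wording on random intercepts, autoregressive errors and random slopes with: the model has fixed effects of group, visit and their interaction, with the planned covariates, and an unstructured 3x3 within-person covariance; it is fitted by REML with a small-sample degrees-of-freedom correction such as Kenward-Roger; no random effects are added.

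This gives each change its own variance, contains every estimable form of the stated model as a special case, and removes the choice by convergence. The cost is two sentences of text and six covariance parameters instead of the fallback's three, estimated from 80−2 = 78 degrees of freedom; the simulations showed no loss of error control. It does not cure the bias of carried-forward values, which is a separate matter.

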### Issues of Engagement in App-Based Mental Health Interventions

Despite their feasibility and empirical support, there are significant concerns regarding treatment engagement in app-based mental health interventions. Enrollment rates are low, with a meta-analysis showing that 8% to 58% of participants never download the intervention app [49]. Even when the app is downloaded, studies show that some users never use it, and those who engage with the app are unlikely to do so more than a few times, showing a decrease in use over time [49,50]. Similarly, attrition rates range from 24% to 53%, with higher rates found in longer programs (ie, more than 8 weeks) [49]. Importantly, programs without guidance (eg, via human coach, automated reminders) seem to lead to even poorer treatment engagement [51]. This limited treatment engagement in app-based mental health interventions is concerning as users may not receive enough treatment dosage to promote behavioral change.

Considering the importance of promoting treatment engagement for the success of app-based interventions, researchers and clinicians have proposed multiple strategies to increase acceptability, improve adherence, and reduce attrition. Among numerous approaches to promote app user engagement, cultivating a sense of guidance and support may be especially effective. Onboarding procedures in which users interact with providers before starting the intervention, asking questions about the intervention, problem-solving potential barriers to engagement, and building a relationship with the team have shown to be associated with higher treatment engagement [52]. Similar procedures in app-based interventions for POC seem to be effective as users can ask questions about the program and request assistance with technology [53]. As a whole, studies show that onboarding procedures decrease treatment attrition in app-based mental health interventions [49].

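### The intention-to-treat analysis fixes last observation carried forward as conservative, which is not generally true, and the planned multilevel model does not need it

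*Protocol article*

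**What the plan says.** The analysis text under Results in the protocol article chooses the model first: "This study will use multilevel modeling, a statistical methodology that allows time-varying predictors and handling dependence among repeated observations". The model has random intercepts and "an autoregressive error structure to account for dependence among repeated measures", and the article says that "our primary interest is in group-by-time interactions corresponding to differential treatment effects".

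Two analyses are then named. For the first: "In intention-to-treat analyses, group comparisons include all patients originally allocated after randomization, regardless of participant adherence to the intervention or withdrawal". The missing-data rule follows directly: "Missing data will be handled using the last-observation-carried-forward method, which is considered a conservative approach". For the second: "In per-protocol analyses, group comparisons include only those participants who completed the treatment as planned originally".

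Under Participants, the sample size allows for an "approximately 24% attrition rate in short-term (ie, 4 weeks or less) mindfulness meditation app trials with at-risk samples".

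The missing-data method and its justification are therefore both stated. They are not details left to a fuller plan.

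**The concern.** LOCF assumes that a participant who leaves never changes again, and it passes the copied score to the model as if it had been measured. Whether that understates or overstates the treatment effect depends on two things unknown in advance: the course of symptoms over the 4 weeks, and the balance of loss between arms. Calling the method conservative without qualification tells the reader that any error runs against the intervention. In several plausible settings it does not.

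The rule governs the intention-to-treat analysis of all three primary outcomes (stress, anxiety, depression). The other named analysis is restricted to those who completed treatment as planned. Neither therefore analyzes the observed data of all randomized participants as they stand. The arms also differ in burden, with daily meditation and reminders in one and waiting for access in the other, so unequal loss is plausible.

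**Working it through.** **Inputs.** From the article: 40 per arm, three assessments, correlation .60 among repeated measures, about 24% attrition. Assumed: outcome SD 1, equal correlation between all visits, straight-line trends and dropout unrelated to outcome unless stated, two-sided 5% tests. The article gives no figure for the effect of LOCF, so there is none to reproduce. At 24% loss, 80 × 0.24 = 19.2, so about 19 posttreatment scores per outcome would be carried forward.

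**Step 1: bias.** The expected LOCF change in an arm is

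(share completing × posttreatment change) + (share lost after midtreatment × midtreatment change) + (share lost before midtreatment × 0).

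*Equal 24% loss, true benefit 0.50 SD, flat control.* With equal risk in each interval, 1 − √0.76 = 0.128 are lost before midtreatment and 0.872 × 0.128 = 0.112 after. The estimate is 0.76 × 0.50 + 0.112 × 0.25 = 0.408. Simulation gives 0.407. If 70% of losses come before midtreatment (0.168 and 0.072), it is 0.76 × 0.50 + 0.072 × 0.25 = 0.398.

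*No true effect, common 0.5 SD trend, 40% against 10% loss, 70% of it early.* Arm with more loss: 0.60 × 0.5 + 0.12 × 0.25 = 0.330. Other arm: 0.90 × 0.5 + 0.03 × 0.25 = 0.4575. False difference: 0.1275 SD. The sign depends on the trend and on which arm loses more.

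*Early gain that fades* (0.5 at midtreatment, 0.2 at posttreatment), flat control, 24% lost in each arm after midtreatment: 0.76 × 0.2 + 0.24 × 0.5 = 0.272 against a true 0.20 (simulated 0.277). If the same loss is spread over both intervals, the simulated estimate is 0.21, so this exaggeration needs late loss.

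**Step 2: false-positive rate.** With a standard error near 0.19, the bias is 0.1275 / 0.19 = 0.67 standard errors. Two-sided rejection is then P(Z > 1.29) + P(Z < −2.63) ≈ 0.099 + 0.004 = 10%. Simulation of LOCF-completed data in a random-intercept group-by-time model (6,000 runs, without the autoregressive term or covariates) gives:

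| No true effect | Loss, intervention/control | False difference | Baseline-to-post contrast | Interaction F test |
|---|---|---|---|---|
| Complete data | 0/0 | none | 4.9% | 4.7% |
| Both worsen 0.5 SD | 40%/10% | 0.13 SD, benefit | 12.1% | 9.6% |
| Both improve 0.5 SD | 10%/40% | 0.13 SD, benefit | 11.8% | 9.1% |
| Both improve 0.5 SD | 40%/10% | 0.12 SD, harm | 11.4% | 9.0% |

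Milder cases, change-score test, no true effect:
- 30% against 18% loss, 0.5 SD trend: bias 0.05 SD, rejection 6.0%.
- 40% against 10% loss, 0.2 SD trend: bias 0.05-0.06 SD, rejection about 6%.
- 24% in both arms, 0.5 SD trend: no bias, rejection about 5%.

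**Step 3: apparent precision.** Complete data: the variance of change is 2 × (1 − .60) = 0.8 and the standard error of the difference is √(2 × 0.8 / 40) = 0.200. Under LOCF with equal 24% loss, the 12.8% lost early have zero change. The control variance becomes 0.8 × 0.872 = 0.697. The intervention variance is 0.697 plus 0.031 from mixing people with different mean changes, or 0.728. The standard error is √((0.697 + 0.728) / 40) = 0.189, below that of complete data. In the control arm the baseline-to-post correlation becomes 0.128 × 1 + 0.872 × .60 = .651.

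**Step 4: observed data instead.** In the equal-loss scenario a likelihood analysis without imputation gave 0.499 with a standard error of 0.221. Its bias was about 0.01 or less in every scenario, including those where dropout depended on earlier observed scores. For comparison, completers alone give √(2 × 0.8 / (40 × 0.76)) = 0.229.

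**The case against.** **LOCF often is conservative.** With equal loss and a steady benefit it shrinks the effect. With both arms improving and more loss in the intervention arm it biases against the intervention: in a rerun of the worst-case split, total rejection was 10.5% but false rejection favoring the intervention only 0.4%. This stands. The fault is the unqualified label, since the other directions are equally possible.

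**The large error rates need an extreme case.** They require both a 0.5 SD common trend and a fourfold imbalance in loss. The article supports neither. Both arms are paid for each questionnaire and both receive the app, and skipping meditation is not the same as skipping a survey. This stands, so the 11% is a worst case.

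**Stronger readings that a reader might infer, and that the article does not support:**
- *That at least 24% loss is expected.* The Introduction does say that "attrition rates range from 24% to 53" percent, but ties higher rates to programs longer than 8 weeks. For this 4-week program, approximately 24% is the planning value and not a floor.
- *That improvement in both arms is likely because participants were selected for elevated stress.* Eligibility is set on race-related stress or perceived discrimination, not on the primary outcomes. The article gives correlations between race-related stress and those outcomes of only .21 to .27, so regression to the mean should be modest.
- *That LOCF understates its own standard error.* In the change-score test the reported standard error (0.189) matches the sampling SD (0.191). The problem is apparent precision around a biased estimate.
- *That LOCF produces false mediation findings.* Only people lost before midtreatment get zero change in both mediator and outcome, a correlation between changes is not an indirect effect, and the mediation analyses are declared exploratory.

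**Conclusion.** The point holds in a limited form. The article fixes LOCF as the only stated missing-data method for the intention-to-treat analysis and justifies it by a property it does not generally have. Under equal 24% loss it attenuates a steady 0.50 SD benefit to about 0.40 SD. Under other assumed trajectories or loss patterns it can create or exaggerate a benefit: about 0.13 SD with about 11% type I error in the worst case examined, and about 5-6% in milder ones.

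These sizes rest on assumed trends, dropout splits and timing. They come from change-score tests and a random-intercept model rather than the full planned model with autoregressive errors and covariates. The direction of the argument does not depend on those details. LOCF is also unnecessary, because the multilevel model already chosen can use every observed visit.

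**What to change.** In the analysis text, delete LOCF and the word conservative from the primary intention-to-treat analysis. State instead that the planned multilevel model will be fitted by restricted maximum likelihood to all observed assessments of every randomized participant, without imputation, and that this is valid if data are missing at random. LOCF may stay at most as a labeled sensitivity analysis. A delta-adjusted or reference-based sensitivity analysis would address departures from missing at random; it is optional.

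The cost is one paragraph of text, a little more programming, and a larger standard error: about 0.22-0.23 SD instead of 0.19 SD at 24% loss. Recruitment and conduct are unaffected.
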